### Study procedures

The PREACT-digital study is currently running and will end in June 2026. Interested patients can choose if they want to take part in PREACT-digital (ie, therapy-accompanying digital phenotyping). Individuals who decide to participate in the PREACT-digital can choose between two study versions. Option 1 (‘the short version‘) consists of a 14-day EMA assessment phase paralleled by passive data collection prior to therapy start (T0) only. Option 2 (‘the long version’) consists of one additional EMA phase after 20 therapy sessions (T20) and one after the end of therapy (if the duration of therapy exceeds 1 year, data are collected 365 days after therapy start; TPost). Passive data are collected in parallel throughout the entire time. Participants enrolled in the short version have the option to switch to the long version after they have completed the first assessment phase. The design of our subproject is depicted in figure 1.

**Figure 1 F1:**
[figure not shown]
Study procedures. EMA, ecological momentary assessment.

Once enrolled in PREACT-digital, participating patients go through an onboarding process with trained research assistants. Together, they instal the required apps and connect the smartwatch. For passive data collection in PREACT-digital, patients receive a state-of-the-art smartwatch (Withings Scanwatch Light), the associated Withings app and a customised study app developed by a German tech-startup, called TIKI-app. The TIKI app (1) serves as an interface to the Withings–API, allowing access to the smartwatch data (2) sends out the EMA questionnaires and (3) collects GPS data.

Participants receive information and materials for study participation and provide additional electronic informed consent via the study app. During the first measurement burst, patients receive an onboarding call from the study team, where they get the option to ask questions and report technical problems. In addition, the acceptability and feasibility of EMA and passive sensing are assessed as part of the onboarding call (see interview guideline on https://osf.io/253nb). Information gathered during the onboarding call is entered into a respective REDCap sheet. Between the active assessment phases, patients receive regular update mails with information about their last EMA completion rate and subsequent study procedures.

To reduce interruptions in data transmission leading to high rates of missing data, we implement weekly data monitoring. We run a script to identify participants who have not provided data for more than 7 days. If GPS and/or passive sensing data are absent for more than 7 days, the respective participants receive an e-mail containing instructions on how to restore data transmission. If data transmission is not restored in the following week, participants are contacted by phone. Reasons for interruptions (ie, app settings, participant forgetting to charge phone) are noted, when available. In addition, all active patients receive a notification on Sunday evenings asking them to open the TIKI-App and check settings to avoid automatic suppression of data collection.

Participants can decide to stop participation in PREACT-digital at any time point. In case of dropout, participants are contacted via mail to assess reasons for dropout.

### EMA assessment schedule

During the 14 days of active assessments, patients receive notifications (‘beeps’) in the TIKI-App on their smartphones eight times a day at quasirandom intervals of 90±30 min. Depending on their individual sleep—wake rhythm, participants can choose to receive beeps between 7.30 and 21.30 or 09.30 and 22.30. The respective questionnaires expire after 30 min. Each EMA assessment contains 30–35 items in total, depending on assessment phase and timing. The order of items was pseudorandomised.

We employ graded reimbursement, as it was shown to increase compliance: participants received at least 20€ per assessment phase, 35€ if they completed at least 90 beeps and 50€ if they completed more than 100 beeps. Thus, participants receive up to 150€ for the EMA assessments, which are paid out as a gift voucher. Moreover, individuals participating in the long version of the study are allowed to keep the smartwatch.

### EMA measures

Table 1 contains an overview of all measures. The whole set of items, including response options and assessment schedules, is provided online. Items are presented in German, but example items were translated to English here to facilitate comprehension for non-German-speaking readers. The following constructs are assessed:

*Affect*: Participants were asked about their current affective state. The 17 items contain the PANAS-X (21) subscales, with additional single items on loneliness, fatigue and shyness. At each prompt, they were asked to rate on a scale from 1 to 7 how much they currently felt the respective affect.*Emotion Regulation*: At each beep, participants were asked to rate the intensity and controllability of their most negative thought since the last beep. Then we assessed the use of different ER strategies since the last beep using a German translation of the Regulation of Emotion Systems (RESS–EMA) scale,^24^ with six items covering reappraisal, rumination, suppression, distraction and relaxation. We implemented an additional item on acceptance.*Situational Context:* Self-constructed. To assess the situational context, we developed a custom measurement. Participants were asked to specify activities they had pursued in the preceding 2 hours from a given set of nine common activities. Participants were able to select multiple options simultaneously. The options were influenced by the DIAMONS scale and a comparable long-term digital phenotyping study.^25 26^ Here, we aimed to find a balance between sparsity of items and a high degree of situational coverage. Subsequently, they were asked to evaluate how much they enjoyed the respective activities.*Social Context:* Self-constructed. Participants were asked if they had social contacts since the last beep (online/ in person/ phone) and how agreeable the contact was.*Significant Events:* Self-constructed. Patients were asked to think about the most important event since the last beep and how pleasant they perceived it.*Physical fitness:* Self-constructed. Participants were asked how physically healthy they had felt today on the last beep of the day.*Therapeutic Agency*: We constructed four items based on the Therapeutic Agency Inventory (TAI)^27^ to assess Therapeutic Agency (TA) in everyday life. The original TAI contains three subscales, covering in-session activities, passivity towards the therapist and out-of-session activities. As we were interested in assessing TA in everyday life, our TAI–EMA items are based on the ‘out-of-session activities‘ subscales and cover cognitive and behavioural aspects of TA.*ECG Control:* During measurement bursts, patients were asked two times day to conduct a resting-state ECG on their Scanwatch. To control for potential confounders influencing the signal, we asked if they had consumed nicotine, caffeine or alcohol or had a heavy meal in the last 30 min.

**Table 1 T1:** Overview of data to be collected

Domain	Construct	Description	Example feature	N items	Timing, Sampling
EMA	Positive and Negative Affect	PANAS-X+item on loneliness	How anxious do you feel right now?	17	Baseline, T20, TPost, all beeps
	Emotion Regulation	RESS–EMA scale+item on acceptance	In reaction to the negative feeling I…tried to breathe deeply	8	Baseline, T20, TPost, all beeps
	Situational Context	Self-constructed	How did you spend the time since the last beep?	1	Baseline, T20, TPost, all beeps
	Social Context	Self-constructed	Did you have social contact since the last beep?	3	Baseline, T20, TPost, all beeps
	Significant Events	Self-constructed	How did you perceive the most significant moment since the last beep?	1	Baseline, T20, TPost, all beeps
	Physical Health	Self-constructed	How physically healthy did you feel today?	1	Baseline, T20, TPost, last beep
	Therapeutic Agency	Constructed based on TAI	Today I have… implemented ideas or tasks from therapy	4	T20, TPost, last beep
	ECG Control	Self-constructed	Did you consume coffee in the last 30 min?	1	Baseline, T20, TPost, third and fifth beep
Sensing	GPS	Raw; TIKI-App	Time spent at home		Continuous; event-based
	Steps	Interval sum; Scanwatch	N steps		Continuous; event-based
	Activity	Scanwatch	Time spent cycling, calories burned		Continuous; event-based
	Heart rate	PPG; Interval mean; Scanwatch	Average heart rate		Continuous; regular 30 s samples
	ECG	Resting-State ECG. Scanwatch	Heart Rate Variability		Baseline, T20, TPost; 2 x daily; 30 s
	Sleep	Aggregate scores; Scanwatch	Time in Bed		Continuous

EMA, ecological momentary assessment; PANAS, positive and negative affect; PPG, photoplethysmography; T20, after 20 therapy sessions; TPost, after therapy end or 365 days if therapy lasts longer.

### Passive sensing data

We use a Withings Scanwatch to collect passive data on sleep, physical activity and heart rate (see table 1 for an overview). The following sensor data are available: for sleep, we have SleepDeepBinary, SleepLightBinary, SleepREMBinary, SleepStateBinary, SleepBinary, SleepInBedBinary and SleepAwakeBinary. They indicate if a user was, for a given time period, in deep sleep, light sleep, REM sleep, any sleep state, asleep overall, in bed (whether asleep or awake) or awake. For physical activity, we have ActivityType, ActiveBinary, RunBinary, BikeBinary, WalkBinary, FloorsClimbed, ElevationGain, ActiveBurnedCalories and Steps. ActivityType contains information on a detected activity in a given time period (ie, resting and walking). The remaining features indicate if, for a given time period, a person was generally physically active, running, biking, walking, how many floors or metres in altitude a person made, how many calories a person burned and the number of steps. Heart rate is collected passively using photoplethysmography (PPG). When no physical activity is detected, the Scanwatch collects heart rate data every 10 min for 30 s and provides the average heart rate for that sampling interval. As soon as physical activity is detected, the Scanwatch collects PPG-based heart rate continuously until the activity stops.

The Withings Scanwatch also allows you to perform 30-s resting-state ECGs (300 Hz) with medical-device quality. During active assessment phases, patients are asked to conduct an ECG on their Scanwatch two times a day. The resting-state ECG data are available in raw format. Withings also calculates Root Mean Square of Successive Differences (RMSSD) for resting-state ECGs as an indicator of HRV.

The TIKI app collects GPS data directly from the mobile phone’s sensor. To increase patient’ privacy and data security, GPS data are anonymised locally before saving them on the study servers by rotating the Latitude–Longitude tuples by a random angle. Like this, only mobility patterns (ie, distance travelled) but not exact locations can be inferred.

### Sample size calculation

As described in the main study protocol,^1^ the required sample size for the PREACT study was estimated (a) using simulation studies with fivefold cross-validation to yield a prediction accuracy of 75–80% and (b) using effect size calculation for group-based linear multiple regression analyses, resulting in a required sample of 585 patients. Of those, it was expected that around 80% would take part in PREACT-digital, resulting in an estimated sample size of 468 patients for T0. Based on previous studies investigating the feasibility of digital phenotyping in clinical samples,^28^ it was further expected that 75% of the sample would decide for the long version of the study, resulting in 350 patients providing data at T20 and TPost.

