### Data preprocessing and feature engineering

In its raw format, passive sensing data are usually not interpretable. Thus, depending on the data source, data format and research question, different data preprocessing and aggregation steps will be necessary.

GPS data are collected as tuples containing coordinates (ie, Latitude and Longitude values). To clean and preprocess the data and build ML features, we follow guidelines by Müller *et al* (35). We adapt them to our event-based sampling format, where GPS was assessed when a location change was detected. From GPS data, we will calculate movement patterns in predefined timescales, that is, location entropy, distance travelled or time spent at home.Passive data derived from the Withings Scanwatch will be further preprocessed where possible and necessary, as Withings does not provide raw data for most data sources (see table 1). Here, we align our preprocessing steps with guidelines for preprocessing sensor data (36). From continuous PPG-based heart ate data, we are able to build features like average HR, min/max HR and HR-zones. From the resting-state ECG,we can create more fine-grained features like HRV. For sleep, we will calculate features describing sleep quality, that is, sleep duration, proportion of sleep phases and sleep efficiency (i.e. sleep duration/ time in bed) per night. Activity features describe the amount of, or time in active or inactive states, that is, total number of steps or time spent walking/running/cycling and the amount of calories burned.For EMA data, we will calculate the RMSSD (that is, for emotional inertia or ER variability), individual SD and mean values. Further feature engineering steps for EMA are described in the *Analysis* section.

Depending on the research question and granularity of data aggregation, a certain compliance rate has to be met to be included in the analysis (ie, at least 50% of completed EMA beeps). Missing data imputation will also depend on the type of data and applied analyses.

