#### Predictive analyses

We will implement both basic and advanced models and compare subsets of data and different timeframes to balance interpretability and predictive performance. With a sample size of at least 350 participants, we have sufficient data to explore a range of methods.

There are various ways to aggregate and preprocess EMA data to include them as predictors of non-response, ranging from simple aggregates to advanced modelling techniques. We will implement dynamic structural equation models (DSEM), an advanced extension of multilevel modelling that integrates time-series dynamics with latent variable modelling.^30^ Multilevel models are considered the gold standard for longitudinal data analysis in psychology,^31^ and DSEM builds on this foundation to allow unequally spaced observations and modelling of time-lagged dependencies, making it well suited for EMA data. The Bayesian estimation approach allows for missing data under the missing at random assumption (eg, when participants skip measurements). Beyond that, DSEM models are extendable to model change in dynamic parameters across measurement bursts. Further, passive data can be flexibly integrated into DSEM to analyse cross-lagged relationships between EMA (ie, affect) and passive sensing features (ie, sleep and physical activity). The model-based framework allows us to derive dynamic parameters (eg, individual autocorrelations and cross-lagged relationships) that we will use as features for the predictive analyses.

For the prediction of NR, basic algorithms include logistic regression, support vector machines, random forests and gradient boosting, depending on the research question and predictors used. Tree-based approaches are known for their effectiveness on tabular data.^32^ Regression-based approaches are highly interpretable. All of the selected require fewer computational resources compared with deep learning models and were frequently applied in psychotherapy research, increasing comparability.^33^,^35^

Advanced modelling approaches will be selected to incorporate the hierarchical, sequential and multimodal structure of our data. These include deep learning architectures like LSTM, Transformers or ensemble learning approaches. To explore how the predictive capacities depend on the time lag, we compare the accuracies of models using subsets of available data (eg, first measurement burst vs second measurement burst) and outcome timepoints (ie, T20 vs TPost).

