## Discussion

Within the research endeavour of the PREACT study to find predictors of non-response to CBT for ID, PREACT-digital implements therapy accompany digital phenotyping. DP complements the other subprojects by contributing dense, behavioural and physiological information from the patients everyday life, providing an ecologically valid and innovative add-on to more traditional sources of data. By integrating EMA with wearable-based passive sensing, we capture detailed, real-time information that goes beyond traditional cross-sectional snapshots. Our predictive analyses aim to determine whether advanced but computationally demanding modelling approaches improve accuracy over simpler methods, while exploratory analyses focus on uncovering potential mechanisms and subgroups that may inform tailored interventions.

A key strength of our study lies in its ecological validity: participants provide data in naturalistic settings, resulting in rich, high-frequency observations. We further benefit from a relatively large sample size and the opportunity to capture change processes over multiple time points. The integration of our project into the Research Unit allows us to compare our digital phenotypes with other data modalities and acquire a rich, comprehensive impression of participating patients. Although a few studies have integrated DP into outpatient therapy settings, this combination of different data modalities is unique to our study.

Despite these strengths, there are also key limitations that demand consideration. First, the study includes no healthy control group. As a result, we cannot directly distinguish digital patterns that are specific to clinical presentations from those also present in non-clinical populations. Future work will need case–control or population-based designs to clarify the specificity of any digital signatures identified here. Second, the extensive assessment schedule may place a burden on participants. Although we tried to keep the length of our active assessments reasonable (ie, around 3–5 min to complete it), answering eight daily questionnaires across 14 days is non-negligible. Also, participants are asked to wear their smartwatch as continuously as possible, also during nighttime. This combination of frequent questionnaires and continuous sensing may reduce adherence over time and, in the worst case, could lead some participants to withdraw from the study.

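### The 350 patients said to provide T20 and TPost data are the expected opt-ins to the long version with no allowance for loss, and the 75–80% accuracy is tied to 585, not to this subproject's own sizes

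*Protocol article*

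**What the plan says.** The Sample size calculation section refers to the main PREACT protocol for two calculations. One was done "using simulation studies with fivefold cross-validation to yield a prediction accuracy of" 75–80%, the other "using effect size calculation for group-based linear multiple regression analyses", together "resulting in a required sample of 585 patients". About 80% of these are expected to join PREACT-digital, which gives 468 at T0. Of those, 75% are expected to choose the long version, "resulting in 350 patients providing data at T20 and TPost". The Abstract gives the same 350 as the number who opt for the long version.

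The Predictive analyses section builds on this figure: "With a sample size of at least 350 participants, we have sufficient data to explore a range of methods". The Introduction sets the subproject's own target, accuracy above 75% for non-response at T20 and TPost from features collected at T0.

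Elsewhere the article names ways in which patients or their data can be lost:
- Sample selection: patients who come to need inpatient treatment are excluded.
- Study procedures: participants may stop at any time.
- Data preprocessing and feature engineering: "a certain compliance rate has to be met to be included in the analysis", with half of the EMA beeps as the example.
- Discussion: the burden "may reduce adherence over time and, in the worst case, could lead some participants to withdraw from the study".

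**The concern.** The 75% is a choice between two study versions. It is not a retention rate. The same product is an opt-in count in the Abstract, a count of patients with data up to a year later in the Sample size calculation, and a minimum in the Predictive analyses. The first and second agree only if essentially nobody is lost, and the third does not follow from either.

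The second part concerns what the sample-size argument supports. The article sets an accuracy target for PREACT-digital and calls its data sufficient, but the only accuracy figure in the sample-size section is attached to a larger study. A reader cannot tell what performance, or what precision on the hold-out set, was expected at 468 or 350.

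At stake are the credibility of the stated size for every model that needs T20 or TPost EMA or in-therapy sensing, and the reader's view of how firmly a result near 75% could be established.

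**Working it through.** **Inputs.** From Sample size calculation: 585, 80%, 468, 75%, 350. From Data freeze, holdout and model training: 20% hold-out. The article gives no attrition rate, so the rates below are assumptions. The 585 itself cannot be reproduced, because its inputs are in the main protocol.

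**1. The plan's own figures.**
- 585 × 0.80 = 468, as stated.
- 468 × 0.75 = 351, against 350 stated (rounding).
- Implied retention from opt-in to TPost: 350 / 351 = 0.997, so no loss factor is present.
- Relative to 585: 468 / 585 = 80% and 350 / 585 = 60%.

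**2. Effect of an allowance for loss (assumed rates).** Remaining = 351 × (1 − d), development = 0.8 × remaining, hold-out = 0.2 × remaining.

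| Assumed loss d | Remaining | Development | Hold-out |
|---|---|---|---|
| 0% | 351 | 281 | 70 |
| 10% | 316 | 253 | 63 |
| 20% | 281 | 225 | 56 |
| 30% | 246 | 197 | 49 |

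Switching from the short to the long version, which Study procedures permits, could offset some of this. The short version would hold 468 − 351 = 117 patients. Ignoring loss among the switchers, full replacement at 10%, 20% and 30% loss would need about 35, 70 and 105 of them (30%, 60% and 90%). No switching rate is given.

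**3. Models that do not need the long version.** Predicting BSI-GSI response from T0 features can include short-version patients, because PREACT itself collects the BSI-GSI (Outcomes). The starting number is then 468. It stays at or above 350 as long as no more than 1 − 350/468 = 25% are lost through missing outcomes or the compliance threshold. At 30% it is 468 × 0.70 = 328.

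**4. Development size and hold-out precision.** Development = 0.8 × N, hold-out n = 0.2 × N, 95% half-width around 75% accuracy = 1.96 × √(0.75 × 0.25 / n).

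| N | Development | Hold-out n | Half-width |
|---|---|---|---|
| 585 (PREACT) | 468 | 117 | 7.8 points |
| 468 (T0) | 374 | 94 | 8.8 points |
| 350 (long version, no loss) | 280 | 70 | 10.1 points |
| 280 (350 with an assumed 20% loss) | 224 | 56 | 11.3 points |

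**The case against.** The case on the other side is substantial, and it limits the point in five ways.

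- **The required size is not met.** A reader might infer this from 468 and 350 being below 585. The article does not support it. The 585 comes from a simulation and a regression calculation together, and the article does not say which one drove it or whether it already includes dropout or a hold-out. The simulation also used fivefold cross-validation, so that split cannot be counted as a further shortfall.
- **350 is a ceiling.** This is also too strong. The 80% and 75% are expectations, switching to the long version is allowed, and T0-feature models with BSI-GSI outcomes can use up to 468. For those models, at least 350 is a defensible reading at moderate loss.
- **The loss can be quantified.** It cannot. The compliance threshold is an example that depends on the research question, the remark on adherence is conditional, and the earlier feasibility study cited in the Introduction is said to show variation by treatment stage without a direction. The plan also has measures against loss: weekly monitoring with e-mail and telephone contact, graded payment, keeping the watch, and a method that tolerates skipped measurements under missing at random.
- **Deep-learning models should be relabelled as exploratory.** That is a preference. They are compared with simpler models and tested on an untouched hold-out set.
- **A condensed article may leave detail to the main protocol.** This is fair for the simulation settings. It does not cover a number that the article itself states and describes differently in three places.

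None of this supplies a loss factor for the 350 or turns an expected opt-in count into a minimum.

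**Conclusion.** The point holds in a limited form. The 350 is the expected number choosing the long version before any attrition, and it is misdescribed as the number with T20 and TPost data and then as a minimum. Any positive loss that switching does not offset makes it too high. The size of the excess cannot be fixed from the article; at assumed losses of 10–30% it is about 35 to 105 patients.

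Separately, the article ties 75–80% accuracy to 585 and shows no performance or precision figure at 468 or 350. This is a gap in the stated justification. It is not evidence that the accuracy is unattainable at those sizes. The half-widths rest on a normal approximation, a true accuracy of 75% and an exact 20% hold-out in the analysed group.

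The correction should be made, because a stated size is not the one the design can be expected to deliver and restating it is cheap.

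**What to change.** 1. In Sample size calculation, state that 585 and 75–80% refer to PREACT overall, that about 468 are expected at T0, and that about 350 are expected to opt for the long version before attrition. Then give the number expected with usable T20/TPost data under an explicit, labelled attrition assumption, and mention possible gain from switching. The 316, 281 and 246 above are illustrations, not expectations to be printed as fact.
2. In Predictive analyses, replace the phrase at least 350 with: about 350 expected to opt in, before attrition, for models needing T20/TPost EMA or in-therapy sensing; up to 468 for T0-feature models with BSI-GSI outcomes.
3. Re-run the existing simulation at the resulting development sizes (about 374 for 468, 280 for 350, fewer after loss) and report the accuracy it gives.
4. State the expected hold-out precision for each type of model: about 8.8 points at 94 patients, 10.1 at 70 and 11.3 at 56.

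The cost is rewording and re-running a simulation that already exists. The stated figures become less favourable. No extra patients are needed.
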